# Non-inferiority, randomised, open-label clinical trial on the effectiveness of transurethral microwave thermotherapy compared to prostatic artery embolisation in reducing severe lower urinary tract symptoms in men with benign prostatic hyperplasia: study protocol for the TUMT-PAE-1 trial

**DOI:** 10.1186/s13063-024-08409-x

**Published:** 2024-09-02

**Keywords:** Benign prostatic hyperplasia, Lower urinary tract symptoms, International Prostate Symptom Score, Patient-reported outcome measures, Prostatic artery embolisation, Transurethral microwave thermotherapy, Minimally invasive surgical therapy, Erectile function, Non-inferiority, Multicentre

## Abstract

**Background:**

One-fourth of men older than 70 years have lower urinary tract symptoms (LUTS) that impair their quality of life. Transurethral resection of the prostate (TURP) is considered the gold standard for surgical treatment of LUTS caused by benign prostatic hyperplasia (BPH) that cannot be managed conservatively or pharmacologically. However, TURP is only an option for patients fit for surgery and can result in complications. Transurethral microwave thermotherapy (TUMT) and prostatic artery embolisation (PAE) are alternative minimally invasive surgical therapies (MISTs) performed in an outpatient setting. Both treatments have shown to reduce LUTS with a similar post-procedure outcome in mean International Prostate Symptom Score (IPSS). It is however still unknown if TUMT and PAE perform equally well as they have never been directly compared in a randomised clinical trial. The objective of this clinical trial is to assess if PAE is non-inferior to TUMT in reducing LUTS secondary to BPH.

**Methods:**

This study is designed as a multicentre, non-inferiority, open-label randomised clinical trial. Patients will be randomised with a 1:1 allocation ratio between treatments. The primary outcome is the IPSS of the two arms after 6 months. The primary outcome will be evaluated using a 95% confidence interval against the predefined non-inferiority margin of + 3 points in IPSS. Secondary objectives include the comparison of patient-reported and functional outcomes at short- and long-term follow-up. We will follow the patients for 5 years to track long-term effect. Assuming a difference in mean IPSS after treatment of 1 point with an SD of 5 and a non-inferiority margin set at the threshold for a clinically non-meaningful difference of + 3 points, the calculated sample size was 100 patients per arm. To compensate for 10% dropout, the study will include 223 patients.

**Discussion:**

In this first randomised clinical trial to compare two MISTs, we expect non-inferiority of PAE to TUMT. The most prominent problems with MIST BPH treatments are the unknown long-term effect and the lack of proper selection of candidates for a specific procedure. With analysis of the secondary outcomes, we aspire to contribute to a better understanding of durability and provide knowledge to guide treatment decisions.

**Trial registration:**

ClinicalTrials.gov NCT05686525. Registered on January 17, 2023, 
https://clinicaltrials.gov/study/NCT05686525.

## Administrative information

Note: the numbers in curly brackets in this protocol refer to SPIRIT checklist item numbers. The order of the items has been modified to group similar items (see http://www.equator-network.org/reporting-guidelines/spirit-2013-statement-defining-standard-protocol-items-for-clinical-trials/).

## Introduction

### Background and rationale {6a}

Benign prostatic hyperplasia (BPH) is a noncancerous enlargement of the prostate gland and a frequent cause of bladder outlet obstruction (BOO) and lower urinary tract symptoms (LUTS) in ageing men. One-fourth of men older than 70 years have moderate to severe LUTS that impair their quality of life (QoL) [1]. The severity of LUTS is measured using quantitative symptom indices, with the International Prostate Symptom Score (IPSS) being the most widely used [2].

The management of LUTS caused by BPH is in many cases initially watchful waiting and non-pharmacological interventions [3]. If the result of conservative management is not satisfactory, pharmacological treatment with alpha-blockers alone or in combination with 5-alpha reductase inhibitors is recommended [3, 4]. Compared to alpha-blocker monotherapy, combined therapy has been shown to reduce the relative risk of BPH clinical progression in men with moderate to severe LUTS [4]. A subset of patients with persisting LUTS will need surgical therapy; transurethral resection of the prostate (TURP) is still regarded as the gold standard [3, 5]. However, TURP requires a spinal epidural or general anaesthesia and can result in complications and adverse events (AEs) such as blood loss, urethral strictures, incontinence, and retrograde ejaculation [6]. Consequently, several less invasive procedures have been developed for men who are not candidates for or do not wish to undergo TURP.

Transurethral microwave thermotherapy (TUMT) and prostatic artery embolisation (PAE) are minimally invasive surgical therapies (MISTs) performed in an outpatient setting without the need for general anaesthesia. Both treatments have proven effective in reducing severe LUTS due to BPH with approximately 10 points on the IPSS after 3 months [7–12]. It is however difficult to compare the effect of the two procedures based on previous research as the selection of candidates for the two treatments varies between studies. TUMT is an ablative technique where a specially designed urinary catheter with a microwave heat antenna is inserted in the urethra and used to destroy hyperplastic prostatic tissue [13]. TUMT has been shown to be an effective alternative to alpha-blockers for treating symptomatic BPH [14]. A study looking at long-term follow-up after TUMT showed that 10% needed additional treatment after 5 years [15]. In PAE, an interventional radiologist embolises the prostate arteries under fluoroscopy guidance [16], causing ischemia of prostatic tissue and consequently shrinkage of the gland. A recent study has shown that PAE provides better urinary and sexual score benefits than combined therapy with a prostate-selective alpha-blocker and 5-alpha reductase inhibitor, in patients with bothersome LUTS refractory to prostate-selective alpha-blocker treatment alone [17]. A study looking at long-term results after PAE has shown that 5 years after treatment 23.6% needed additional LUTS treatment [18].

To date, PAE has not been compared to TUMT in a randomised clinical trial [19]. In the TUMT-PAE-1 trial, the primary objective is to assess the effectiveness of the reduction in the IPSS of PAE compared to TUMT for the treatment of BPH. A challenge with MIST BPH treatment is the lack of guidance when selecting candidates for each procedure [10]. The secondary outcomes after short- and long-term follow-up, including side effects, functional outcomes, and QoL, are selected to provide information that could guide treatment options in the future.

## Objectives {7}

The primary objective of this trial is to investigate the non-inferiority of PAE to TUMT in reducing LUTS 6 months post-procedure. The secondary objective is to compare LUTS (IPSS), patient satisfaction with the treatment, QoL (International Prostate Symptom Score—Quality of Life (IPSS-QoL), EQ-5D-5L and BPH Impact Index (BII)), health economics (EQ-5D-5L), erectile function (International Index of Erectile Function—Erectile Function (IIEF-EF)), ejaculatory function (Danish Prostatic Symptom Score—sexual questions (DAN-PSS-1-sex)), incontinence (International Consultation on Incontinence Questionnaire—Urinary Incontinence Short Form (ICIQ-UI-SF)), uroflowmetry outcomes, post-procedure duration of catheterisation, prostate volume (PV), prostate-specific antigen (PSA) and creatinine, incidence of side effects, de novo use of pharmacological LUTS treatment, and surgical re-treatment rates of TUMT and PAE during the 5 years following the procedures. The objective of this comparison is to create a reference for clinicians in patient counselling when choosing a MIST for the treatment of BPH.

## Trial design {8}

This study is designed as a pragmatic multicentre, non-inferiority, open-label randomised clinical trial comparing the effectiveness of TUMT versus PAE in reducing the symptoms of BPH. A non-inferiority design has been chosen as the treatments are expected to perform similarly in effectiveness. If non-inferiority is demonstrated, the analysis of our secondary outcomes will be able to support decision-making for the individual patients needs when choosing a MIST for the treatment of BPH. PAE will be tested for inferiority with TUMT as the reference. PAE is expected to be inferior to TUMT by + 1 point on the IPSS within the non-inferior margin allowing the favour of TUMT of + 3 points in the IPSS. Patients will be randomised with a 1:1 allocation ratio between the two treatments.

## Methods: participants, interventions, and outcomes

### Study setting {9}

The TUMT-PAE-1 trial will be performed at academic hospitals in northern Europe. Eight centres are planned to be included in the trial.

From the Capital Region and Region Zealand of Denmark, the included hospitals are Rigshospitalet, Herlev and Gentofte University Hospital, and Zealand University Hospital. From the Region of Southern Denmark, we expect to include Odense University Hospital, and from the Central Denmark Region, Aarhus University Hospital. We hope to also include Helsingborg Hospital and Karolinska University Hospital in Sweden and Oslo University Hospital in Norway.

### Eligibility criteria {10}

We have kept the eligibility criteria to a minimum for a pragmatic framework to reflect real-life patient populations.

#### Inclusion criteria

Men ≥ 40 years.Ability to understand and the willingness to sign an informed consent.Diagnosis of LUTS secondary to BPH refractory to/contraindicated for medical treatment or patient preference for TUMT/PAE.Severe urinary symptoms on IPSS (IPSS ≥ 20), an indwelling catheter, or intermittent catheterisation. In the last two cases, the baseline IPSS is set to 35 points.A maximum flow rate (Qmax) ≤ 15 mL/s.Prostate volume at minimum 50 mL measured by transrectal ultrasound measurement (TRUS) or MRI.

#### Exclusion criteria

Active bladder cancer with any other grading than pTa low-grade.Prostate cancer on any other treatment plan than active surveillance or watchful waiting.Previous pelvic radiation.Bladder stones (inclusion is allowed after removal).Current urethral stricture or bladder neck contracture.Neurogenic LUTS.Documented bacterial prostatitis in the last year.Severe atherosclerotic vessels or other pathology preventing catheter-based intervention (as rated on computerised tomography angiography (CTA) by an interventional radiologist).Allergy to iodinated contrast media.Renal failure, defined as eGFR < 35 mL/min.High bleeding risk, defined as spontaneous INR > 1.6.Contraindication to conscious sedation (if requested by the patient).Large prostate median lobe as defined by the treatment physician.Urethral colliculus to bladder neck length < 35 mm.

### Who will take informed consent? {26a}

Patients referred with LUTS due to BPH with urinary obstruction planned to be treated with a MIST will be evaluated for eligibility to participate in the study by the treatment-responsible physicians at the participating departments of urology. After the assessment of the patient’s eligibility, relevant study material will be provided to the patient. If the patient gives oral consent, the treatment-responsible physician will pass on the necessary personal information to the principal investigator (PI) at the respective centre. The patient will be invited for a screening visit with the research physician to discuss any questions and sign the informed consent. The patient will be offered a minimum of 24 h of decision time. If the patient wishes a prolonged decision period, a new appointment will be arranged.

### Additional consent provisions for collection and use of participant data and biological specimens {26b}

N/a. No further consent is needed since no biological material will be stored after analysis.

## Interventions

### Explanation for the choice of comparators {6b}

No standard of care exists for the included patient group. Current research indicates that TUMT and PAE are two MISTs with similar results in the efficacy of reducing LUTS. Thus, the clinical decision about which treatment is offered to the patient is settled at each treatment centre. Alternative treatments, which may be offered to the TUMT or PAE patient group, include transurethral water vapour thermal therapy (Rezūm), clean intermittent catheterisation, or surgery with general anaesthesia/spinal epidural including TURP or open/robot-assisted prostatectomy (a.m. FREYER).

### Intervention description {11a}

The patients will be managed according to operating procedures for TUMT and PAE at each centre. Both procedures are conducted under local anaesthesia in the outpatient department. Usually, the patient can be discharged from the hospital on the same day. If the patient cannot be discharged on the same day, he will be admitted to the urological ward. Below is a general description of the two procedures.

#### Arm 1: TUMT

TUMT is performed by a urologist and/or a trained urological nurse. In TUMT, a specially designed instrument that sends out microwave energy is inserted inside the prostate through the urethra. Cooling fluid circulates the instrument to prevent heat from damaging the wall of the urethra. To prevent the temperature from getting too high outside the prostate, a temperature sensor is positioned around the penis and inside the rectum. If the temperature reaches the safety limit, the microwave generator’s output will shut off automatically. Utilising the ProstaLund CoreTherm Device (ProstaLund, Lund, Sweden) microwave delivered by ProstaLund Feedback Treatment is used to heat the prostate at a range of 50–60 °C, destroying hyperplastic prostate tissue. As the prostate heals, it will shrink, reducing the blockage of urine flow and the symptoms of BHP. After the treatment, a transurethral catheter is inserted. This will be removed at the physician’s discretion when spontaneous voiding is achieved with an acceptable residual volume (generally < 150 mL), typically within 4 weeks.

#### Arm 2: PAE

In PAE, an interventional radiologist will insert a small catheter into the vessels that supply blood to the prostate. Habitually arterial access is reached by a unilateral femoral sheath placed in the right common femoral artery under local anaesthesia. Digital subtraction angiography of the pelvic arteries is performed to assess the origin points of the internal iliac arteries and to map the vessels feeding the prostate. Pelvic arterial anatomy is complex and prostatic arteries exhibit a noticeable variation of origin, are often duplicated, and provide collaterals to the opposite half of the prostate and nearby structures. In addition, they are often markedly tortuous, making catheter advancement difficult. Cone beam computed tomography can be applied to assure correct placement or prevent non-target embolisation. Tiny embolisation particles are injected through the catheter and into the blood vessels to reduce the blood supply to the prostate. This procedure is intended at both sides of the prostate. Following the procedure, the prostate will shrink reducing the symptoms of BPH. A transurethral catheter is inserted before the procedure. In patients without a permanent catheter before PAE, this will be removed after the procedure. Patients with a permanent catheter before PAE will keep the catheter until spontaneous voiding is achieved with an acceptable residual volume (generally < 150 mL), typically within 4 weeks.

### Criteria for discontinuing or modifying allocated interventions {11b}

The patient can withdraw the informed consent and leave the study at any time without explanation. If the patient withdraws consent, no further data will be collected. The data already collected until that point will be stored and used for study purposes. If the patient requests to change the treatment option after randomisation, he will be referred to his respective department of urology for his preferred treatment option and included in the analysis as intention-to-treat. The study can be closed prematurely if any untoward patient complication is observed in either treatment arm, defined as serious adverse events (SAEs) resulting in organ failure or death.

### Strategies to improve adherence to interventions {11c}

N/a. As the interventions are surgical and performed as one-time procedures, no strategies to improve adherence were formed.

### Relevant concomitant care permitted or prohibited during the trial {11d}

As a pragmatic study, any concomitant care that the treating physician finds relevant is permitted during the trial but will be registered.

### Provisions for post-trial care {30}

The patients will be followed for 5 years at the urological research unit at the respective centre; any need for ancillary or post-trial care will be looked after.

### Outcomes {12}

The outcome measures used in this trial generally follow the registry network for surgical treatment of BPH recently developed [20]. The primary outcome is the mean IPSS of the TUMT and PAE arm 6 months after the procedure. The IPSS is a validated, reproducible, patient-reported outcome measure (PROM) to assess LUTS severity and response to treatment. This measure was selected as the primary outcome as it is the most clinically relevant and internationally accepted PROM for assessing LUTS [21].

The secondary outcomes include the following:The mean IPSS of the two arms at all other follow-up occasions than the primary outcome.The mean procedure time for the conduction of TUMT and PAE as well as the calculated necrosis.Health-related quality of life measured by the mean IPSS-QoL, BII, and EQ-5D-5L. IPSS-QoL assesses the quality of life associated with symptoms from urinary problems. The BII is a self-reported, validated, disease-specific instrument for quantifying the interference of LUTS on the patient’s mental health and activity. As a measure of QoL, it is used to determine treatment outcomes in men with symptomatic benign prostatic hyperplasia [22]. The EQ-5D is the most widely applied instrument for health-economic assessment worldwide. Its index values are used in the estimation of quality-adjusted life year gains in economic evaluations of healthcare interventions [23].Mean satisfaction with treatment by a five-level bipolar Likert scale.Erectile function measured by the mean IIEF-EF score. The IIEF-EF domain score is a PROM used to measure erectile performance and assess disease severity in efficacy trials. It distinguishes between men with and without erectile dysfunction (ED), classifies levels of ED severity, and has the requisites to detect treatment-related changes in patients with ED [24, 25].Ejaculatory function measured by the mean DAN-PSS-1-sex. The DAN-PSS-1-sex is a validated instrument to determine erectile and ejaculatory function and its impact on the well-being of the patient [26].Incontinence measured by the mean ICIQ-UI-SF. The ICIQ-UI-SF is validated for evaluation of the frequency, severity, and impact on QoL of urinary incontinence [27].Mean prostate volume (PV) measured by TRUS in mL.Mean uroflowmetry outcomes of the two arms. We will be looking at voided volume, Qmax, and residual urine. Uroflowmetry is a non-invasive procedure used to measure the flow of urine throughout micturition. It provides useful information about the total voiding function and is used for diagnosis of lower urinary tract dysfunctions and evaluation of treatment response. Qmax is the value of the highest flow rate measured during the test; it will be set to zero if the patient has an indwelling catheter. Transabdominal ultrasound will be used to assess post-voided residual urine as it is accurate and non-invasive [28].Post-procedure catheterisation events, including the placement of an indwelling urinary catheter and the use of intermittent catheterisation. Catheterisation will be expressed as the reason for placement, duration, and frequency (in case of intermittent catheterisation). If an indwelling catheter is placed after the procedure, the post-procedure duration of catheterisation will be defined as days from the procedure till indwelling catheter cessation. Catheterisation for any other reason during the follow-up period will also be evaluated.Prostate-specific antigen (PSA) and creatinine. The absolute value of serum PSA (ng/mL) has a good predictive value for the determination of prostate volume. Continued PSA measurements assist in the detection of any de novo prostate cancer or progression of patients in active surveillance or watchful waiting. A rise in serum creatinine can be a result of BPH with urinary retention. Serum creatinine aids in the identification of any affection of the kidney from the procedures.De novo use of pharmacological LUTS treatment and surgical re-treatment rates will be collected from the patient’s health record.Incidence at 3 months post-procedure of urinary tract infection, acute urinary retention, dysuria, haematuria, post-embolisation syndrome (PES), hospital admission, and hospitalisation time. PES is defined as occurring within 48 h after surgery and consisting of influenza-like symptoms, pelvic pain, nausea, dysuria, or transient worsening of LUTS. Data on AEs and side effects will be collected from the patient’s health record and the follow-up visit at 3 months. Surgical complications will be categorised following the Clavien-Dindo grading [29].

In Table 1, the specific time points for collection of secondary outcomes can be appreciated.

**Table 1 Tab1:** Time schedule

Visit	Screening	Intervention	FU 1	FU 2	FU 3	FU 4	FU 5	FU 6
Day	− 365 to − 2	0	1 month (± 5 days)	3 months (± 14 days)	6 months (± 14 days)	1 year (± 14 days)	2 years (± 14 days)	5 years (± 14 days)

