**Screening activities**								
Informed consent	**X**							
Inclusion/exclusion	**X**							
Randomisation	**X**							
Demographics	**X**							
Medical history	**X**							

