##### Follow-up management

Patients will be followed for 5 years post-procedure, with a total of four follow-up visits to the outpatient clinic at 3, 6, 12, and 24 months. The results from the long-term follow-up at 5 years will be completed with digital PROMs and assessment of the patient’s health record. Outcome data will be collected in accordance with Table 1. To complete the procedures and PROMs for the follow-ups at 3 months to 5 years, a 28-day window will be allowed, defined as 14 days before and 14 days after the due date. For the 1-month follow-up, the permitted window will be 10 days, 5 days before and 5 days after the due date.

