### Sample size {14}

A non-inferiority study design was chosen based on several case studies on the efficacy of TUMT and PAE in men with similar inclusion criteria as this trial. From a review of TUMT, a study with a baseline IPSS above 19 and follow-up after 3 months was selected [30]. In this study, the IPSS 12 weeks after TUMT had decreased to 11.3 with a standard deviation (SD) of 6.3 [8]. With PAE, a recent independent study has demonstrated an IPSS at baseline of 19.4 with an SD of 6.3. Twelve weeks after the procedure, the IPSS declined to 10 with an SD of 6.5 [7]. The difference of approximately 1 IPSS point between the two treatments holds for 6- and 12-month follow-up according to the data available in systematic reviews [10, 12, 31]. Due to resource constraints of our trial and the great variation in SD across TUMT and PAE trials, we have chosen an SD of 5 [30, 32]. The sample size calculation was based on “Sample sizes for clinical trials with normal data. *Statist. Med.* 2004; 23:1921–1986” by Julious [33]. The size was calculated using the package “PowerTOST” in R for the sampleN.noninf() function in R set to parallel design. We used a one-sided significance level of 0.025. Power was set at 80%. Assuming a difference in mean IPSS after treatment of + 1 point in the favour of TUMT with an SD of 5 and a non-inferiority margin set at the border for a clinically non-meaningful difference of + 3 points in the favour of TUMT [34, 35], the calculated size was 100 per group, giving a total size of 200 patients. Dropouts are defined as patients who after inclusion are lost to follow-up for the primary outcome. To compensate for an anticipated dropout rate of 10%, the study will include 223 patients.

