### Concealment mechanism {16b}

REDCap allocates the patient when baseline measures have been completed and the informed consent signed, in that way the allocation concealment will be guaranteed.

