### Methods in analysis to handle protocol non-adherence and any statistical methods to handle missing data {20c}

The study is analysed as intention-to-treat. As data is expected to be missing completely at random, missing data will be handled by pairwise deletion.

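### The primary IPSS is timed from the procedure but men are randomised at screening, so a randomised man who is never treated has no 6-month assessment and drops out of an analysis called intention-to-treat

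*Protocol article*

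**What the plan says.** Table 1 of the protocol article lists "Randomisation" in the Screening column, whose window runs from day −365 to day −2, with the intervention at day 0. Concealment mechanism {16b} gives the trigger: "REDCap allocates the patient when baseline measures have been completed and the informed consent signed". Nothing there ties allocation to a booked procedure.

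The endpoint starts later. Outcomes {12} states: "The primary outcome is the mean IPSS of the TUMT and PAE arm 6 months after the procedure". The Follow-up management text, which counts its visits in months, has the same origin: "Patients will be followed for 5 years post-procedure, with a total of four follow-up visits to the outpatient clinic at 3, 6, 12, and 24".

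On the analysis set, section {20c} says "The study is analysed as intention-to-treat" and then "As data is expected to be missing completely at random, missing data will be handled by pairwise deletion". Section {11b} covers a man who asks to change treatment after randomisation: "he will be referred to his respective department of urology for his preferred treatment option and included in the analysis as intention-to-treat". Sample size {14} adds: "Dropouts are defined as patients who after inclusion are lost to follow-up for the primary outcome". No section says when, or whether, a man who stays in the trial but has no procedure completes the primary IPSS.

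**The concern.** An intention-to-treat comparison needs an outcome date for every randomised man. Here the date is created by an event after randomisation, the procedure, which some men may not reach. The schedule asks such a man for no 6-month IPSS, and the missing-data rule then deletes him. The analysed set is defined partly by what happened after allocation.

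Men and staff know the allocation during the wait. TUMT is done by a urologist or urological nurse and PAE by an interventional radiologist, so waits and refusals could differ between arms. The documents do not show that they do. If they do, deletion is not harmless. An untreated man presumably keeps most of his symptoms, so removing more such men from one arm makes that arm look better. In the PAE arm, that works towards a false finding of non-inferiority.

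**Working it through.** **The plan's own figure.** Inputs from Sample size {14}: margin 3, SD 5, true difference 1, one-sided alpha 0.025, power 80%.
- Normal approximation: n per arm = 2 × 5² × (1.960 + 0.842)² / (3 − 1)² = 98.1, so 99.
- Exact noncentral t: power is 79.97% at 99 per arm and 80.4% at 100 per arm, so 100 per arm.
- Dropout: 200 / 0.9 = 222.2, so 223.

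The stated size reproduces and does not depend on the time origin.

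**Timing.** Table 1 allows screening at day −365 to −2 and the 6-month visit at ±14 days. Taking 6 months as 183 days, the primary IPSS can fall from 2 + 183 − 14 = 171 to 365 + 183 + 14 = 562 days after randomisation. For a man without a procedure it falls nowhere.

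**What happens to each kind of man under the text as written.**
- Treated as allocated: has a day 0 and is analysed.
- Switches to the other study procedure: has a day 0 and stays in his allocated arm under {11b}.
- Switches to a treatment outside the trial: intention-to-treat is stated, but it is undefined whether that treatment counts as the procedure for timing.
- Has no procedure: no day 0, no 6-month IPSS, deleted under {20c}.

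**Bias (illustration).** Let u be the never-treated proportion in an arm, and let untreated men score D points higher than treated men. Then approximately:

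difference in all randomised men = difference in treated men + D × (u_PAE − u_TUMT).

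The Background section gives a fall of about 10 points after either treatment, so take D = 10, which assumes that untreated men do not improve. The gap u_PAE − u_TUMT is an assumption. The standard error is 5 × √(2/100) = 0.707. If the true difference in all randomised men is exactly +3, the one-sided error is Φ(−1.960 + hidden shift / 0.707).

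| Gap, PAE minus TUMT | Hidden shift | Error at the margin |
|---|---|---|
| 0 | 0 | 2.5% |
| +2 points | 0.2 | Φ(−1.677) = 4.7% |
| +4 points | 0.4 | Φ(−1.394) = 8.2% |
| +8 points | 0.8 | Φ(−0.829) = 20.4% |
| −4 points | −0.4 | Φ(−2.526) = 0.6% |

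The two source studies had post-treatment SDs of 6.3 and 6.5. At SD 6.4 the standard error is 0.905, and the +4 row becomes Φ(−1.518) = 6.5%.

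**Numbers.** If never-treated men come on top of the 10% dropout, 5% of them leave 223 × 0.9 × 0.95 = 190.7 evaluable men (power 78.5%), and 10% leave 180.6 (76.2%). The loss of power is modest; the bias matters more.

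**The case against.** The strongest reply is that the gap is narrow and could be closed in the full protocol or statistical analysis plan, neither of which is shown. The 365 days are a permitted maximum, not an expected wait. No wait or never-treated rate is given by arm. The 10% dropout allowance may already include untreated men.

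Part of this stands: the number affected is unknown and may be small. But an analysis plan cannot recover a score that the visit schedule never requests, and a dropout allowance restores numbers without removing bias.

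A reader might also infer more than the documents support:
- *That every man who departs from his allocation is lost.* Section {11b} keeps switchers in the intention-to-treat analysis, and those who have the other study procedure have a 6-month date.
- *That men found unsuitable for PAE are lost after allocation.* CT angiography is a screening procedure and unsuitable vessels are an exclusion, so much of this is settled beforehand. An attempted procedure that fails arguably still has a date.
- *That deaths show the fault.* A man who dies before the assessment has no IPSS under any time origin.
- *That a year-old baseline IPSS biases the result.* It is measured before allocation, so it is balanced in expectation however long each arm waits. Its age costs precision in the ANCOVA but does not bias it.
- *That the bias must favour PAE.* More untreated men in the TUMT arm would make deletion conservative.

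**Conclusion.** The point holds for men who receive no procedure. For them, the schedule and deletion rule as written contradict the intention-to-treat statement, and for men treated outside the trial the time origin is undefined. This does not show that the whole intention-to-treat analysis fails, or that a bias will occur.

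The size is conditional: about 0.4 IPSS points hidden, and a one-sided error of about 8% instead of 2.5%, if the PAE arm has 4 percentage points more never-treated men. This rests on an untreated-to-treated contrast of 10 points, SD 5, 100 analysed per arm, and a gap for which the documents give no figure. The hidden shift is proportional to the gap and reverses with its sign. Because the planned analysis gives no sign of such a shift, and scores not collected on time cannot be obtained later, the plan should be changed.

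**What to change.** 1. Define day 0 as the first BPH procedure of any kind after randomisation, inside or outside the trial.
2. For a randomised man with no procedure, set a default day 0 by a stated rule, for example the planned procedure date, or randomisation plus the site's median wait.
3. Send him the same digital questionnaires 6 months after that date, unless he has withdrawn consent, and include him in the primary analysis under his allocated arm.
4. Report the randomisation-to-procedure interval and the number never treated, by arm.

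The cost is a scheduling rule in REDCap, a few lines of protocol text and a conventional assessment date for what may be few men. The questionnaires and reminders are already digital. Enrolment began in October 2022, so any untreated man whose default date has already passed should be counted and reported as missing. Allocating closer to the procedure would also shorten the gap, but it changes the workflow at up to eight centres mid-trial and is optional.
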